### Study Design and Objectives

In this pilot study, we aimed to evaluate the administration of 2 different synbiotic formulations compared to placebo in newborns in PNG during the first week of life. The study design was a double-blind, randomized, placebo-controlled trial in which newborns received 1 of 2 synbiotic formulations or a placebo over 7 consecutive days, with the first dose given before the newborn was aged 72 hours and administration completed within the first 10 days of life. The overall objective is to generate data that will inform the design and implementation of a larger, definitive clinical trial in infants in PNG, including the assessment of clinical end points.

The primary pilot study objectives were (1) safety in terms of intolerance (diarrhea, vomiting, abdominal distension, and weight gain) or probiotic sepsis during the 7-day supplementation period, leading to the cessation of the study medication; and (2) the feasibility and cultural acceptability of daily probiotic administration (the proportion of children who received all 7 daily doses of supplementation without missing any). The secondary objective was to demonstrate the colonization of the gut by probiotic strains at age 1 week and at ages 1, 3, 4, and 6 months. The exploratory objectives included (1) hospitalization rates until age 6 months, (2) nasopharyngeal carriage of *Streptococcus pneumoniae* and other respiratory tract bacteria at age 2 weeks and at ages 1 and 4 months, (3) immunoglobulin G (IgG) antibody responses to childhood vaccination (PCV13; diphtheria, tetanus, and whole-cell pertussis [DTwP]; *Hemophilus influenzae* type b [Hib]; and hepatitis B), (4) the kinetics of probiotic colonization at various time points over the first 6 months of life, and (5) maternal carriage and colonization by probiotic species and pathogens at the time of delivery.

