**Exclusion criteria**
Mother HIV positive or of unknown statusMother with foul-smelling amniotic fluidHeavy meconium staining of amniotic fluidMother with fever (>38 °C) within −2 or +2 d of deliveryMother with abdominal tenderness within 2 d of deliveryParents unable or unwilling to provide consentInfant receiving antibiotics between birth and screening (within the first 72 h of life)Infant with signs or symptoms of suspected infection at the time of screeningInfant with a major congenital abnormalityInfant with an Apgar score of <8

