### Intervention Administration, Vaccination, and Follow-Up

The schedule of synbiotic administration, routine infant vaccinations, and specimen collection throughout the study is shown in Figure 1. Just before administration, a single vial of intervention product corresponding to the appropriate day of administration (d 1-d 7) was diluted by adding 3 mL of either breast milk or sterile water directly to the vial, followed by inverting 5 times to mix and resuspend the contents. The resulting suspension was administered to the infant in oral drops using a Pasteur pipette, similar to the method used for oral polio vaccine. Before administration, infants were breastfed and burped. The intervention was administered by PNGIMR study staff (HEO or study nurse). When the intervention was administered at participants’ homes, the product vials were transported in small portable coolers with ice packs. The infant was monitored for 30 minutes after receiving the intervention. In cases of vomiting, the dose was repeated an hour later. A missed dose was defined as any scheduled daily dose (d 1-d 7) not administered on the same day, regardless of the reason, including participant unavailability, vomiting without readministration, or logistical barriers to follow-up. During the observation period, infants were taken to the PNGIMR clinic for examination and treatment (if the intervention had been administered elsewhere) and referred to Goroka Provincial Hospital when necessary. Obstetrics information and baseline characteristics were obtained on the day of enrollment. At each follow-up visit, the infant’s health was reviewed before any intervention administration, vaccination, or specimen collection. Weight and length measurements were recorded, and information on feeding practices was also collected at each visit.

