### Statistical Analyses

The data will be cleaned before analysis. All data will be downloaded from REDCap and a backup copy archived before data cleaning. Missing data, outliers, and inconsistencies will be queried and verified against source documentation. Where data require changing, the database will be updated accordingly. All queries and corresponding amendments will be documented. Per-protocol and intention-to-treat analyses will be performed using available outcome data. The distribution of missing data across the treatment groups will be described, and reasons for missingness will be explored where possible to assess whether data are missing at random.

The primary objective is to determine the feasibility and safety of treatment. The number of solicited and unsolicited adverse events as well as the number of discontinued, missed, and completed doses will be summarized descriptively by treatment group. Pearson chi-square and Fisher exact tests will be used as appropriate to determine the significance of differences between groups.

The secondary objective is to measure gut colonization by probiotic strains on the last day of treatment (d 7-d 10) and at ages 1, 3, and 4 months. The prevalence of colonization at each time point will be summarized descriptively by treatment group. Colonization status, categorized as positive or negative, will be compared between treatment groups using the Pearson chi-square test, while continuous measures of colonization (ie, cycle threshold or relative fluorescence units) will be analyzed using 1-way ANOVA.

The exploratory objectives include measuring the hospitalization rates throughout the study; nasopharyngeal carriage of *S pneumoniae* and other respiratory bacteria; IgG antibody titers to PCV13, DTwP, Hib, and hepatitis B; the kinetics of probiotic gut colonization; and maternal carriage of probiotic species at the time of delivery.

Hospitalization rates will be reported descriptively per treatment group and compared using Pearson chi-square or Fisher exact tests as appropriate.

Nasopharyngeal carriage of *S pneumoniae* and other respiratory bacteria as well as gut colonization will be summarized descriptively at each corresponding time point. A Cox regression analysis will be performed, adjusting for birth weight, sex, previous antibiotic use, and breastfeeding status. Hazard ratios, along with their 95% CIs and *P* values, will be reported.

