IgG antibody titers to PCV13, DTwP, Hib, and hepatitis B will be reported descriptively at baseline (before vaccination at age 1 mo) and at age 4 months (1 mo after the third dose). The differences between treatment groups will be estimated using linear regression, adjusting for birth weight, sex, breastfeeding status, and previous antibiotic use at each time point. The model will also adjust for maternal antibody titers to diphtheria, tetanus, and pertussis when comparing IgG titers to DTwP, using prevaccination infant titers as proxy measures. All IgG levels will be log transformed before analysis to meet the normality assumptions of linear regression analysis. The corresponding coefficients, along with their 95% CIs and *P* values, will be reported.

Maternal vaginal carriage of probiotic species will be reported descriptively and compared using the Pearson chi-square test.

Ad hoc analyses will include comparisons of IgG antibody levels, nasopharyngeal carriage of respiratory bacteria, SAEs, and other growth outcomes between participants colonized and those not colonized by *B longum* subspecies *infantis* or *L plantarum*. The Pearson chi-square test, the Fisher exact test, and regression modeling will be used as appropriate. The models will adjust for the variables specified earlier.

To ensure that normality assumptions are met before parametric testing, tests for normality (eg, the Shapiro-Wilk test) and a visual assessment of distribution using histograms will be carried out and the results reported. Where necessary (eg, antibody titers), the raw data will be log transformed to achieve a normal distribution.

The results of the analysis will be reported according to the CONSORT (Consolidated Standards of Reporting Trials) guidelines.

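### The exploratory between-arm models for carriage, colonization and IgG adjust for infant antibiotic use that can arise only after randomisation, and possibly for feeding status measured after it

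*Protocol article*

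**What the plan says.** Two adjusted between-arm models appear under Statistical Analyses in the protocol article. For nasopharyngeal carriage and gut colonization: "A Cox regression analysis will be performed, adjusting for birth weight, sex, previous antibiotic use, and breastfeeding status". For IgG at 1 and 4 months, group differences come from linear regression, "adjusting for birth weight, sex, breastfeeding status, and previous antibiotic use at each time point".

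Four other statements bear on when these covariates are fixed:

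- The exclusion criteria remove an infant "receiving antibiotics between birth and screening (within the first 72 h of life".
- Study Design and Objectives describes a seven-day course, "with the first dose given before the newborn was aged 72 hours".
- Intervention Administration, Vaccination, and Follow-Up says "Obstetrics information and baseline characteristics were obtained on the day of enrollment".
- The same section adds that "information on feeding practices was also collected at each visit".

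Statistical Analyses also promises intention-to-treat as well as per-protocol analyses.

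**The concern.** A covariate in a randomised comparison should be fixed before the treatment can act on it. Infant antibiotic use in this trial is not. The trial's rationale is that synbiotics may prevent infection: Study Rationale and Objectives cites an Indian trial with less sepsis, respiratory infection, diarrhoea and omphalitis. Fewer infections would mean fewer antibiotic courses. Morbidity Surveillance goes further, since an admission with a planned antibiotic course of five days or more itself counts as a severe infection.

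Conditioning on such a variable can do two things. It can remove the part of the effect that runs through antibiotics. If infection-prone infants also differ in carriage or titre, it can also create an association between arm and that proneness which randomisation had excluded. In either case the coefficient or hazard ratio no longer has to equal the intention-to-treat effect.

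For carriage and IgG, these adjusted models are the only between-arm estimators the article describes. The trial is meant to inform the design of a larger one, so a shifted estimate could be carried forward.

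**Working it through.** **Timing of the antibiotic covariate.** Use between birth and screening is an exclusion, so it is nil for every infant at entry. The first dose is due before 72 hours of age. The IgG outcomes are at 1 and 4 months, and the carriage swabs at 2 weeks, 1 month and 4 months. If the term means the infant's own use, it is either a constant, which adjusts for nothing, or it was acquired after randomisation.

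**Timing of the feeding covariate.** Entry requires oral feeding, not breastfeeding. Infants are described as breastfed at dosing ("Before administration, infants were breastfed and burped"), but exclusive and mixed feeding could still differ at enrolment. Feeding is recorded at every visit, and no sentence says which value enters the models.

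**Size.** The article gives no rate of antibiotic use and no effect of antibiotics on titre or carriage, so there is no stated figure to reproduce. The planned 50 per group rests on an unadjusted test of proportions and does not change. What follows is an illustration for log IgG in SD units; every input is assumed except the sample size. Table 1 shows 178 infants at 4 months, so 178/3 ≈ 59 per arm.

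Without shared frailty:

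- total effect = direct effect + (antibiotic rate on product − rate on placebo) × effect of antibiotics
- the antibiotic-adjusted model estimates the direct effect only

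Take a direct effect of 0.30 SD and antibiotic use of 40% on placebo, halved to 20% on product:

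- antibiotics lower titre by 0.5 SD: total = 0.30 + (−0.20)(−0.5) = 0.40; share removed = 0.10/0.40 = 25%
- antibiotics lower titre by 0.3 SD: total = 0.30 + (−0.20)(−0.3) = 0.36; share removed = 0.06/0.36 ≈ 17%

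Simulation (ordinary least squares, 59 per arm, 2,000 runs per row) agrees and adds shared frailty. Frailty is a standard normal variable that raises the log-odds of antibiotics and shifts titre; with frailty, the rates shown are those at average frailty.

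| Antibiotic use, placebo → product | Antibiotic effect on titre (SD) | Direct effect (SD) | Frailty (log-odds; titre) | Mean unadjusted | Mean adjusted | Rejection, unadjusted → adjusted |
|---|---|---|---|---|---|---|
| 40% → 20% | −0.5 | 0.30 | none | 0.398 | 0.298 | 57% → 36% |
| 40% → 20% | −0.3 | 0.30 | none | 0.364 | 0.304 | 50% → 36% |
| 30% → 21% | −0.3 | 0.30 | 0.5; 0.3 | 0.323 | 0.311 | 42% → 39% |
| 40% → 40% | −0.5 | 0.30 | none | 0.298 | 0.299 | 34% → 35% |
| 40% → 20% | 0 | 0 | 0.5; 0.3 | 0.005 | 0.033 | 5.0% → 5.0% |
| 40% → 20% | 0 | 0 | 1; 0.5 | −0.001 | 0.072 | 5.0% → 6.6% |

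The second row gives (0.364 − 0.304)/0.364 ≈ 16%, which matches the 17% above within simulation error. In the last two rows there is no true effect and the adjusted difference is spurious; its sign follows the assumed sign of frailty on titre.

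For scale, the standard error of an arm difference is √(2/59) ≈ 0.18 SD.

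For carriage the direction could reverse. If antibiotics clear carriage, a product that spares antibiotics raises carriage by that path, and adjustment would remove a component working against the product.

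**The case against.** The strongest reply is that the article does not define its terms. Previous antibiotic use could mean maternal peripartum use, which is not an exclusion and would precede randomisation. The phrase about each time point could describe when the models are fitted, not time-updated covariates. A full analysis plan may settle both. This stands as a reason to ask for a definition. It does not rescue the text as written: maternal antibiotics are nowhere mentioned as a covariate, and infant use cannot be a baseline variable under the eligibility rules.

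The second reply is that the effect may be negligible. That stands in part. The spurious differences of 0.03 to 0.07 SD are well below one standard error, and there is no bias at all if the product leaves antibiotic use unchanged. For feeding, no passage says that the product alters breastfeeding, and blinding makes that path weak.

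Four stronger readings are tempting, and the document does not support them:

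- A reader might infer that both covariates can vary only after randomisation. For feeding this is not established, because oral feeding is the only requirement at entry.
- A reader might infer that the main results are compromised. The feasibility, safety and hospitalization comparisons use chi-square or Fisher exact tests, and secondary colonization uses chi-square or ANOVA, all unadjusted. The adjusted models serve exploratory aims in a pilot.
- A reader might infer that most of the effect is lost. That requires assuming that almost the whole effect runs through antibiotics, which nothing in the document shows.
- A reader might extend the point to the ad hoc comparisons of colonized with non-colonized infants. Those groups are not randomised, and antibiotic use may be a legitimate confounder there.

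**Conclusion.** The point holds for infant antibiotic use in the two exploratory between-arm models. By the trial's own eligibility rule it is a post-randomisation variable, it plausibly lies on the infection pathway, and conditioning on it means that the reported estimates need not equal the intention-to-treat effect. For breastfeeding status the fault is narrower: the text leaves open the use of values measured after randomisation.

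This is a risk, not a demonstrated distortion, and the document does not allow its size to be computed. Under assumed inputs, the loss ranges from none (antibiotic use unchanged) through about 4% (0.012/0.323, the mild case) to roughly 16% to 25% (antibiotic use halved from 40%, with antibiotics lowering titre by 0.3 to 0.5 SD). The conclusion assumes that the term refers to the infant's own use.

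**What to change.** Under Statistical Analyses, define the covariates of the between-arm Cox and IgG models by when they are measured:

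- Keep birth weight and sex.
- Drop infant antibiotic use. An enrolment value would be a constant, so substituting one achieves nothing. If maternal peripartum use was meant, say so and use that.
- Take feeding status as recorded at enrolment.
- Report models with antibiotic use or feeding status after randomisation only as sensitivity or mediation analyses, labelled as not estimating the total effect of assignment.

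An enrolment carriage result cannot be added to the carriage model, because nasopharyngeal swabs start at 2 weeks. The ad hoc colonized-versus-not models need not change.

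The cost is a wording change, which the article's description of the analysis as ongoing would still allow. Intervals may widen slightly if antibiotic use or later feeding is strongly prognostic. No sample-size figure changes.

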### Morbidity Surveillance

All serious adverse events (SAEs) that occurred during the study period were recorded. The variability in diagnostic terms and a lack of gold standard case definitions for neonatal sepsis make it difficult to compare incidence, severity, etiology, or disease outcomes across studies and settings. Therefore, instead of sepsis, we examined “severe infection” as a clinical outcome, acknowledging that many infants will not manifest overt signs of sepsis and using the qualifier “severe” to indicate that localized infections without systemic features (eg, skin pustules) will be excluded. Severe clinical infection was defined as the presence of at least one of the following signs or symptoms to align with a similar study of synbiotics in Bangladesh [31]: (1) poor feeding (not sucking effectively or not sucking at all, as directly observed), (2) lethargy (movement only when stimulated or not moving at all, as directly observed), (3) convulsions (observed or strongly suspected by the clinician based on caregiver or community health worker report), (4) severe chest in-drawing (observed), (5) fever (axillary temperature of ≥38 °C), and (6) hypothermia (axillary temperature of <35.5 °C). In addition, any subsequent positive sterile site cultures or hospitalization with intention to treat with antibiotics for at least 5 days was considered indicative of severe clinical infection.

Throughout the study, the pediatric ward at Goroka Provincial Hospital was monitored daily for possible admissions of study infants. For any participant admitted, clinical information on health status, reason for admission, treatment, and discharge outcomes was recorded. In addition, parents or guardians were encouraged to bring their infants to the PNGIMR clinic for any illness experienced to enable SAEs to be recorded during this period. If clinically indicated, specimens were collected to aid in health assessment and diagnosis. Clinical samples included small volumes of blood (approximately 2 ml), stool, and a nasopharyngeal swab. Samples were processed at the PNGIMR laboratory, and the results were returned to the study clinicians for dissemination to the participant’s parent or guardian.

If a child was unwell during a scheduled study visit, routine procedures such as intervention administration and sample collection were still conducted unless contraindicated.

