### Specimen Collection

For the secondary and exploratory objectives of the study, a number of biological samples were collected at several time points throughout the study (Figure 1). Rectal swabs and stool samples were collected to assess intestinal colonization by probiotic species. Rectal swabs were collected at enrollment; on the day of the last intervention administration (age 7-10 d); and at ages 2 weeks, 1 month, 3 months, 4 months, and 6 months. For sample collection, the infant was carefully placed face down across the mother’s thighs. A FLOQSwab (Copan Diagnostics) was gently inserted approximately 2 cm into the anal canal, rotated slowly for 10 seconds, then removed and placed into a tube containing eNAT preservation and transport medium (Copan Diagnostics). The swab was broken at the breakpoint, leaving the tip in the tube, which was then sealed and mixed by inverting 10 times. Stool samples were collected in addition to rectal swabs if infants passed stool during the study visit to allow for sensitivity comparisons of probiotic strain detection in rectal swabs versus stool. Stool samples were taken from infants’ diapers using a scoop and placed into stool specimen containers for storage and transportation. Upon arrival at the PNGIMR laboratory, stool samples were transferred to cryovials by laboratory staff. Both rectal swabs and stool samples were then stored at −80 °C.

Nasopharyngeal swabs to assess bacterial carriage and load were collected at ages 2 weeks, 1 month, and 4 months using FLOQSwabs. At each time point, 2 swabs were collected per infant when possible. For each collection, a swab was inserted horizontally into the nostril to collect a superficial mucosal sample from the anterior nares, advancing gently until resistance was met. The swab was then rotated while counting to 5 (or for approximately 3 s) before being removed. One swab was placed in skim milk tryptone glucose glycerol broth (STGGB) for culturing of bacterial pathogens (priority), and the second was stored in PrimeStore molecular transport medium (Thermo Fisher Scientific) for deep sequencing. Both samples were stored at −80 °C.

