### Sample Size Calculation

It was determined that a sample size of 50 participants per group would achieve 90% power to detect a difference in colonization rates of 30% in the probiotic group versus 5% in the placebo group, using a 2-tailed test of proportions with continuity correction at the 5% significance level. A final sample size of 65 participants per group was decided upon, taking into account a presumed 10% loss to follow-up and difficulties in timely biosample collection. On the basis of this sample size, it was estimated that the study would have 80% power to detect a 50% reduction in pneumococcal colonization rate in the probiotic group versus the placebo group at the 5% significance level.

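### The comparisons by colonization status leave randomized arm out of their stated adjusters, and set no order between swab and SAE, so they can show an association when colonization has no effect

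*Protocol article*

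**What the plan says.** The last part of Statistical Analyses in the protocol article describes the ad hoc analyses as follows: "comparisons of IgG antibody levels, nasopharyngeal carriage of respiratory bacteria, SAEs, and other growth outcomes between participants colonized and those not colonized by". That sentence closes by naming the two study species as alternatives. On method the article says: "The Pearson chi-square test, the Fisher exact test, and regression modeling will be used as appropriate". On covariates it says: "The models will adjust for the variables specified earlier".

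The variables named earlier in that section are those of the Cox model for carriage and colonization, "adjusting for birth weight, sex, previous antibiotic use, and breastfeeding status", and those of the IgG regression, "adjusting for birth weight, sex, breastfeeding status, and previous antibiotic use at each time point". For DTwP, the prevaccination infant titer is added. Treatment group appears in none of these adjuster lists.

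Three other sections bear on the point:

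- **Sample Size Calculation** assumes "colonization rates of 30% in the probiotic group versus 5% in the placebo group".
- **Specimen Collection** gives seven sampling times. It states: "Rectal swabs were collected at enrollment; on the day of the last intervention administration (age 7-10 d"), and then lists 2 weeks and 1, 3, 4 and 6 months. The ad hoc text does not name the swab that defines status.
- **Morbidity Surveillance** states: "All serious adverse events (SAEs) that occurred during the study period were recorded".

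**The concern.** Colonization status arises after randomization and depends strongly on arm, so a contrast by status is partly a contrast between arms. The arms differ in more than live bacteria. Study Interventions gives 150 mg of fructo-oligosaccharide in one active vial and 1.2 g of 2′-fucosyllactose in the other, while placebo is maltodextrin alone. An effect of the prebiotic, or of bacteria that act without being detected, would appear as an effect of colonization. The chi-square and Fisher tests adjust for nothing, and the regressions as listed do not adjust for arm.

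SAEs raise a second problem. They accrue from enrollment to 6 months, so an SAE can come before the swab that sets status. If the illness or its treatment lowers later detection, infants who were ill move into the not-colonized group and colonization looks protective.

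These comparisons are the only described analysis that relates colonization to immune and clinical outcomes, and Study Design and Objectives says that the pilot is meant to inform a larger trial.

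**Working it through.** **1. The plan's own colonization figure.** The stated size is 50 per group for 30% v 5%, 90% power, two-sided 5%, with continuity correction.

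- Unpooled variance: n = (1.960 + 1.282)² × (0.30×0.70 + 0.05×0.95) / 0.25² = 43.3. Continuity correction: (43.3/4) × [1 + √(1 + 4/(43.3×0.25))]² = 51.0.
- Arcsine form with continuity correction: 49.6, so 50.
- Exact power of the Yates-corrected test at 50 per group: 0.899.

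The figure reproduces under standard variants and is not disputed. It is used below for the 30% and 5%.

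**2. Bias from leaving out arm (IgG, one species).** Inputs: three equal arms; species detected in 30% of its own arm (from the plan) and in 5% of each other arm (plan figure for placebo, assumed for the other active arm); colonization has no effect; the product shifts log IgG by δ = 0.4 SD by another route (assumed). Then

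bias = δ × [P(own arm | colonized) − P(own arm | not colonized)].

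| Own-arm colonization | Own-arm share, colonized | Own-arm share, not colonized | Difference | Bias |
|---|---|---|---|---|
| 30% (plan) | 0.30/0.40 = 0.750 | 0.70/2.60 = 0.269 | 0.481 | 0.19 SD |
| 50% (assumed) | 0.50/0.60 = 0.833 | 0.50/2.40 = 0.208 | 0.625 | 0.25 SD |

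**3. False-positive rate.** Take 59 infants per arm, 177 in all (Table 1 has 178 at 4 months). The standard error is about √[σ²/(N p q)], where p is the overall share colonized and σ² is about 1.03.

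- 30%: p = 0.40/3 = 0.133; N p q = 20.5; SE = 0.224; 0.19/0.224 = 0.86; rejection about 14%. Simulation gives 13%.
- 50%: p = 0.60/3 = 0.20; N p q = 28.3; SE = 0.19; 0.25/0.19 = 1.31; rejection about 26%. Simulation gives 26%.
- With arm in the model, simulation gives bias of about 0 and error of about 5% in both cases.
- With δ = 0 and no arm term, error is nominal, about 5%.

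**4. If either species counts as colonized.** Positive infants then come from both active arms. With only one product active (0.4 SD) and 30% in each active arm, the difference in shares is 0.30/0.65 − 0.70/2.35 = 0.164. The bias is 0.07 SD with 6.8% false positives. At 50% it is 0.09 SD and 8.5%. If both products act, by 0.3 or 0.5 SD, simulation with 178 infants gives 0.08 or 0.14 SD and 7.3% or 11.8% at 30% v 5%.

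**5. SAEs before the swab.** The article gives no SAE rate and no effect of an SAE on detection, so both are assumed. The simulations use 244 infants, six post-dose swabs, 30% positive per swab in the active arms and 5% on placebo, no effect of colonization, and unadjusted tests.

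| Assumption | Status used | False positives |
|---|---|---|
| SAE cuts later detection to a third | ever positive, or positive at 4 months | about 19–21% |
| Same, 15% SAE risk, no losses | ever positive | 24% (risk ratio 0.69) |
| Detection lost completely after an SAE (upper bound), 10–30% SAE risk, no losses | ever positive | 17–74% |
| Complete loss, as above | last-dose swab, later SAEs only | 2.4–5.5% |

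The size depends on the SAE risk, the definition of status and the losses assumed. Counting only SAEs after the swab removes the distortion.

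**The case against.** The strongest objections, and what stands of each:

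- **These are ad hoc analyses.** They rank below the primary, secondary and exploratory objectives, and adverse events, hospitalization and IgG are compared by randomized arm elsewhere in the section. This stands, and it limits the importance. It does not remove the bias from an analysis whose outcomes, tests and adjusters are written down.
- **Arm may be implied.** Treatment group is the exposure in the earlier models, so a generous reader could count it among the variables specified earlier. The adjuster lists do not name it, and the wording does not secure it.
- **The arm bias needs an effect outside colonization.** This stands. Without one, leaving out arm does no harm. The 26% also needs 50% colonization, whereas the plan's own 30% gives 13%.
- **Silence on the swab is normal in a condensed article.** This stands. The full protocol or SAP may fix the swab and the order of events, so the timing point is a condition to secure and not an error of text. The adjuster list is stated and does not depend on it.
- **Previous antibiotic use is adjusted for.** In the regressions this may take out part of the route from SAE to lost colonization. The chi-square and Fisher tests do not adjust, and the simulated SAE figures describe only those unadjusted tests.

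A reader might infer more than the documents support. Loss to follow-up alone might seem to bias the comparison, since infants who leave early have fewer swabs and less time at risk. That needs an ever-colonized definition, which the article does not use. Even then error is about 3–9%, and with status at a single swab it is 4.2–4.6%. A reader might also infer that these comparisons will decide the strain for the larger trial; the article does not say so.

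**Conclusion.** The concern holds in a limited form. The comparison by colonization status is non-randomized, and its stated adjusters omit the variable that most strongly predicts status in the design.

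For IgG, under an assumed 0.4 SD effect of one product outside colonization, the species-specific coefficient is biased by about 0.19 SD with 13% false positives at the plan's 30% v 5%, rising to 0.25 SD and 26% at an assumed 50% v 5%. The bias is smaller if either species counts and zero if there is no such effect. For SAEs, a false protective association with about 20% false positives is possible, but this rests on an assumed loss of detection after an SAE and on a status read after some SAEs have occurred. Timing matters less for IgG at 4 months if an early swab is used.

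The documents do not support reading this as a flaw in the trial's main results: feasibility, safety, colonization and vaccine responses by randomized arm are untouched.

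**What to change.** Three changes to the ad hoc paragraph:

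1. Include randomized arm in every model that uses colonization status, or compare colonized with not-colonized infants within the active arm that received the matching species. State whether status is species-specific or either species.
2. Name the swab that defines status and relate it only to SAEs, carriage, growth and IgG observed after it, among infants still followed. Use the last-dose swab (age 7–10 d) as one landmark and a later swab, for example 1 month, as a sensitivity analysis. The later swab is needed because qPCR on the day of the last dose may detect product just given.
3. Report the results as observational associations.

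This takes a few lines of text and no new data; the article describes the data analysis as still ongoing. The cost is precision. Events before the landmark are not used, and infants who colonize later count as not colonized at an early landmark. If nearly all infants in an active arm are positive at the chosen swab, status almost coincides with arm. Little contrast is then left once arm is in the model, and the report should say so.
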